### 1.2. Theoretical Background to the Study

The theoretical premise of this feasibility study is underpinned by social cognitive theories [27] These theories are the most cited for health behaviour change interventions [28]. In these theories, there is a triad relationship between personal and environmental factors with behaviours being explored through individual level factors such as self-efficacy, stages of readiness for behavioural change and school related autonomy. In self-efficacy theory [29] there are four sources; mastery accomplishments, vicarious experiences, verbal persuasion and physiology are strong predictors of behaviour. Novice learners, such as students in TY, tend to have low confidence to promote PA at the beginning of the year [30]. When schools express their interest to be an SLASF school, a resource pack (see methods section) would support these students to improve the self-efficacy (opportunities for mastery accomplishments), create timetabled meetings with the purpose to focus on the SLASF (opportunities for vicarious experiences) and regular contact with others who are also carrying out the SLASF (opportunities for verbal persuasions), the sources of self-efficacy may create a better suited environment for promoting PA. 

Being autonomous in making decisions is known to be directly related to intrinsic motivations towards a behaviour [31]. However, in the school context, students may feel their overall autonomy is restricted to the bounds of the school. As a result, some students may find the school environment something that they can thrive in, whereas others may feel the environment restricts individual choices. The autonomy supportive environment is as important as having autonomy among school-aged children because it can lead to greater levels of PA outside of the school context [32]. Factors that may influence the autonomy or autonomy support can include the perception of school academic performance and the way teachers and peers support academic performance [33], perceptions of ability to make decisions in the school [34] and feelings of belonging in the school [35]. Furthermore, it has been reported that individual well-being is associated with individual’s sense of autonomy [36], therefore studies may need to consider the mediating factors of student well-being. 

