### 2.8. Data Analyses

#### 2.8.1. Quantitative Data

The data from the surveys are analysed through relevant statistical methods for the follow up data in this feasibility study. Compatible data between comprehensive and basic surveys can be used to determine the test-retest reliability of the items given that a smaller subsample of the entire school. As reliability is an important psychometric property for question items, this is carried out during the first phase of data collection. 

Students take part in the comprehensive study have their measures taken two times during the academic year. The first time takes place in autumn 2018 and the second takes place six months later during the spring 2019. Accelerometer data are transferred through the ActivPal software based on 15sec epoch. The standardised cut-offs for different types of motion; sleep, standing, light, moderate and vigorous PA are then compared at an individual level from pre- and post-test time points. Similarly, the height, weight and grip strength data is compared between the time points and used to control the differences in accelerometer data. Comprehensive survey data is also analysed with differences in PA and school related factors. 

Exploratory approaches include cross-sectional multivariate analyses of PA and school-related factors as independent variables and device-based PA and perceptions of PA opportunities as the dependent variables. Mixed models and multi-level regression analyses can be used on the data that has sufficient follow up data from the first time point. The multi-level approach takes into account between- and within- individual processes that explain variances in the outcome measures. Through this approach, it is possible to test the extent of PA (psychosocial variables) and school-related factors in relation to changes in PA levels and opportunities, at the same time to examine the individual versus the school factors that contribute to the outcome variables. 

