The follow-up data adds another level of analysis that can test the changes through the intervention. It makes it possible to examine, for example, the changes in PA levels across the schools from the beginning and the end of the study, while also taking into account changes in the psychosocial variables included in this study. The interactions between the contexts can confirm behavioural change theories by examining the mediating and moderation mechanisms in PA levels. The majority of the statistical analysis would be carried out using IBM SPSS. 

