	ASF logbook entries	Notes that report barriers to completing actions that are not manageable
	PA audit	Low level of usage when compared with the beginning of the year

**Table 2 jfmk-04-00016-t002:** Aligning outcomes with measures.

SLASF Target Areas	Measures of Efficacy	Details
Physically educated	Self-efficacy in PA	Student survey
Physically active school community	Comprehensive Survey and focus groups	Survey item and discussions
Broad physical education	Whole-school survey and focus groups	List of physical education activities and discussions
Balanced physical education	Teacher scheme of work	Teacher records
More inclusiveness	Teacher scheme of work	Teacher records
Partnership with others to promote pa culture	TY logbook	Taster session from ASW
Active school week	TY logbook	Record of entries
Increased concentration	Harter scale	Student survey
Improved learning	Teachers perceptions	Student and teacher survey
Maintenance of discipline	Teacher records	Discipline records
Improved test results	Winter and summer test	Academic records
School enjoyment	Questionnaire	Student survey
Increase Daily PA	Accelerometers	Comprehensive Data
Reduced sitting time	Accelerometers	Comprehensive Data
Reduction in overweight and obesity	Self-report and anthropometric measures of height and weight	Comprehensive data

**Table 3 jfmk-04-00016-t003:** Battery of questionnaires.

Battery	Items	Response Scales	Psychometric Information
PA Screening measure	2 items on number of days in a week of at least 60 min of MVPA per day	0–7 days	Validity & Reliability [5,44]
PA opportunities	Modified items about local opportunities for PA to the context of schools instead of ‘residential area’	5 point scale, 1 = disagree a lot, 5 = agree a lot	Original items used from an interview guide.
The exercise self-efficacy scale for adolescents	10 items on confidence to participate in a variety of conditions	11 point sliding scale, 0 = not at all confident, 10 = very confident	Nigg & Courneya, 1999 [45]
PA peer support scale	4 items on the frequency of peers influence for PA	0 = never, 5 = every day	Prochaska et al., 2002 [46]
PA, plans, expectancy and intention	Modified 3 items on the planning, expectancy and intention to do PA in the coming week	1 = unlikely, 8 = likely	Hagger et al., 2001 [47]
Readiness for behaviour change	Single item to determine which stage of the transtheoretical model in terms of PA	Select one item of each stage of the transtheoretical model	Lee et al., 2001 [48]

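### Pre-post accelerometer differences are to be controlled for height, weight and grip strength measured at both visits, so the adjusted figure need not be the actual change in physical activity

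*Protocol article*

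**What the plan says.** All of the following is in the protocol article.

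- **Section 2.8.1, direct comparison.** Students in the comprehensive part are measured in autumn 2018 and again six months later. The accelerometer categories "are then compared at an individual level from pre- and post-test time points".
- **Section 2.8.1, adjustment.** The next sentence says that "the height, weight and grip strength data is compared between the time points and used to control the differences in accelerometer data". It stands before the paragraph on exploratory approaches and carries no exploratory label.
- **Section 2.8.1, psychosocial variables.** Further on, PA change may be examined "while also taking into account changes in the psychosocial variables included in this study". This is offered as an example, and the following sentence gives the aim as "examining the mediating and moderation mechanisms in PA levels".
- **Table 2.** Programme targets include "Increase Daily PA", measured by accelerometer, and "Reduction in overweight and obesity", measured by self-report and by measured height and weight. "Self-efficacy in PA" is listed as a measure of efficacy. Grip strength is not listed.
- **Section 2.2.1.** The control schools were recruited for the survey component.

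Nothing limits the adjustment to baseline values, and nothing says whether the adjusted or the direct comparison is the programme's result.

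**The concern.** The variables said to do the controlling are those compared between the two visits, so the natural reading is that follow-up values or changes enter the model. This raises two problems.

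First, weight status is an outcome that the programme hopes to move, and a student whose activity rises may change weight because of it. Conditioning PA change on weight change then conditions one outcome on another, possibly on its own consequence.

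Second, adolescents grow over six months whether or not there is a programme. With no control group for the accelerometer data, the quantity of interest is the average change itself. Putting growth into the model can move that average to a hypothetical student who did not grow. This second problem applies to height even though the programme cannot plausibly alter height.

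At stake is the meaning of a secondary efficacy result: a reader may take an adjusted change as the observed change in daily PA.

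**Working it through.** The plan gives no figure to reproduce: no slope, no expected growth, no expected PA change and no standard deviation. The check is therefore algebraic.

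**Notation.** For each student, D is the PA change from autumn to spring and G is the change in one covariate (height, weight or grip strength). With several covariates, the last terms below become sums.

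**1. Direct comparison.** The estimate is mean(D), the change that occurred in the students measured.

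**2. Change-score model.** Fit D = a + b·G + error by least squares. The fitted line passes through the means, so

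a = mean(D) − b·mean(G).

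The intercept a is the PA change at G = 0, that is, for a student with no growth or weight change. It equals mean(D) only if b = 0 or mean(G) = 0.

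**3. Time-varying model.** Fit PA at each visit on a student effect, a spring indicator with coefficient t, and the covariate value at that visit with slope b. Differencing the two visits gives D = t + b·G + error, so t = mean(D) − b·mean(G), as in step 2. Centring the covariate on its overall mean does not help, because that constant cancels in the difference.

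**4. Centred change score.** Replace G by G − mean(G). The intercept is again mean(D), so the overall average survives. A contrast between two schools or year groups does not: its adjusted value is the raw difference in mean(D) minus b times the difference in mean(G). It shifts whenever the groups grew by different amounts and b is not zero.

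**5. Baseline covariates only.** Fit D = a + c·(B − mean(B)) + error, where B is the autumn value. Then a = mean(D). No variable affected by the programme enters, and the estimate refers to the students actually measured.

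**6. Size and direction.** The gap in steps 2 and 3 is −b·mean(G). The documents give neither b nor mean(G). If students gain weight on average (mean(G) > 0) and those who gain more have the less favourable PA change (b < 0), the gap is positive and the adjusted change exceeds the actual one. If b > 0, the gap is negative. The shift can go either way.

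**Which step applies.** The wording does not settle whether changes, follow-up levels or repeated values enter. The readings in steps 2 and 3 fit a sentence about data compared between time points. Step 5 does not follow from it.

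**The case against.** Several points against the concern stand.

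- The direct comparison is stated one sentence earlier, and the plan never calls the adjusted result its headline. The fault is that no estimate is named, not that the plain one is missing.
- The sentence does not fix the model terms, and an article may leave these to a fuller document. With mean-centred change scores the overall average would be unaltered (step 4).
- Without accelerometer controls, allowing for growth is an understandable attempt to deal with maturation. It does not achieve that: ageing, season and programme remain mixed in the before-after change, and the adjustment only changes the student to whom the figure refers.
- Height is not plausibly affected by the programme, and grip strength is not a Table 2 target. The argument about conditioning on an outcome rests on weight.
- The models with psychosocial changes serve a stated mediation aim, for which conditioning on such changes is proper. The theory passage in section 1.2, where "the sources of self-efficacy may create a better suited environment for promoting PA", concerns Transition Year students' confidence to promote PA. It does not by itself make the surveyed self-efficacy scale a mediator of pupils' PA.

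A reader might infer two stronger things. One is that the adjustment removes the programme's effect, or a definite part of it. In a two-group model, adjusting for a mediator that carries a share s of the effect leaves 1 − s of it. The documents give no s, nothing in them makes height, weight or grip strength a carrier of the effect on PA, and without accelerometer data from control schools there is no group coefficient to shrink. The other is that the distortion reaches the decision on a randomised trial. Table 1 contains no accelerometer criterion, and its limited-efficacy row uses the comprehensive surveys with no covariate adjustment mentioned.

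**Conclusion.** The concern holds in a limited form. As written, section 2.8.1 controls pre-post accelerometer differences for variables measured after the programme has started. One of these, weight, underlies a programme outcome, and the plan does not say whether the adjusted or the direct comparison is the programme's result. Under a change-score model with uncentred covariates, or a time-varying model, the adjusted figure differs from the actual mean change by the slope times mean growth. The documents do not allow that amount, or its sign, to be stated.

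This rests on two readings: that the phrase about comparison between time points means follow-up values or changes enter the model, and that section 2.2.1 confines control schools to the survey. The second is probable but not certain, because Table 4 gives comprehensive-arm numbers for the control schools too (123, 121 and 88). The consequence is for the interpretation of a secondary efficacy result, not for the primary feasibility objective.

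**What to change.** Reword section 2.8.1 as follows.

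1. Name the pre-post change in accelerometer PA, without post-baseline covariates, as the programme estimate. Describe it as a before-after change if control schools provide no accelerometer data.
2. If adjustment is wanted, use baseline values only, for example baseline height, weight, grip strength, sex and year group, centred so that the mean change is preserved.
3. Analyse changes in weight status and in grip strength as outcomes in their own right.
4. Report models containing changes in height, weight or grip strength, and models containing changes in psychosocial variables, only as exploratory mediation analyses and not as the programme's effect.

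The cost is a few sentences. The autumn visit already supplies the baseline measurements, so no new data, visits or students are needed.

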### 2.2. Recruitment

#### 2.2.1. School Recruitment

The SLASF programme is a comprehensive programme and employs a whole school approach. As an intervention programme, schools were invited to take part if they are not currently in the process of obtaining the Active School Flag. The normal process of the SLASF recruitment is for schools to make an application but this was suspended to allow time to develop the new model. Schools that were interested in carrying out the feasibility study contacted the Active Schools office and requested to pilot the second level programme. There were three schools that responded and accepted because they each have a strong well-being structure in place in their schools. This is a feasibility study with secondary outcomes on efficacy hence matched control schools (one girls only, one mixed and one mixed DEIS school) were recruited to take part in the survey component of the study. No reserve list was formed for this cohort but engagement of all three schools throughout the year to follow the feasibility and evaluate the SLASF process.

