#### 2.2.2. Student Recruitment

In the participating schools, there are two levels of student engagement—basic and comprehensive. Although all students are exposed to the same SLASF programme, those engaged in the SLASF Basic are required to complete less data collection measures than those in the SLASF Comprehensive. The whole school is involved in the SLASF Basic and a random class from each year group is selected to take part in the SLASF Comprehensive. Classes are known as mixed ability tutor groups. Students obtain their consent to take part in the study. Even though there may be some students who do not obtain consent or would not like to withdraw from the comprehensive aspect of the study, there is no likely reason for them to influence the feasibility of the study. 

The SLASF initiative is structured to fit into the TY framework providing real and meaningful opportunities for student voice and youth leadership. A TY class would be nominated by the school as the SLASF TY class. This TY class attends classes in relation to SLASF tasks including youth leadership, mentoring and PA promotion. 

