### 2.4. Allocation Strategy

There was no allocation strategy used to select the schools. As a feasibility study, it was important to test the SLASF in various contexts. Three contexts were chosen; a DEIS school, a girls only school and a mixed school. All schools are considered to be large in size and this would test out the possible whole-school approach. 

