### 2.7. Sample Size

There are three schools that are part of the feasibility study. Unlike a sample size calculation, a justification is made for feasibility studies [53]. In Table 4, information about the size of the school, the type and the number of participants expected to complete the comprehensive arm of the study is presented. 

According to the Department of Education and Skills school lists, School B is one of the largest secondary level in Ireland, with 1313 enrolled students. It is also a DEIS school. Approximately 10% of secondary level students attend a DEIS designated school. Moreover, there are known socioeconomic barriers towards PA [6], therefore it is necessary to carry out this feasibility in a DEIS school environment. School A is an all-girls school. Almost one in five schools in the country are all-girls’ schools. There are many reports of girls having lower levels of PA than boys and therefore it is essential to include an all-girl’s school. School C has a slightly fewer number of students than the national average of 999 students per school. Moreover, the ratio between girls and boys is slightly higher for girls (1:1.05), whereas the national average in mixed schools tends to have fewer girls than boys (1:0.87). 

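### The exploratory multi-level model is credited with separating school from individual factors, which three schools (six for surveys) cannot support at school level; the sampled tutor group is also not among the levels named

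*Protocol article*

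**What the plan says.** Section 2.8.1 of the protocol article introduces exploratory analyses with "device-based PA and perceptions of PA opportunities as the dependent variables". It then says: "Mixed models and multi-level regression analyses can be used on the data that has sufficient follow up data from the first time point". Of these models it states: "The multi-level approach takes into account between- and within- individual processes that explain variances in the outcome measures". It adds that they make it possible "at the same time to examine the individual versus the school factors that contribute to the outcome variables". The closing paragraph of the section offers a comparison of activity change across schools. It also says that interactions between contexts can confirm behaviour-change theories through mediation and moderation.

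The design behind these statements is set out elsewhere:

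- Section 2.7: "There are three schools that are part of the feasibility study".
- Section 2.4: "Three contexts were chosen; a DEIS school, a girls only school and a mixed school".
- Section 2.2.1: "matched control schools (one girls only, one mixed and one mixed DEIS school) were recruited to take part in the survey component of the study".
- Section 2.2.2, on the comprehensive sample: "a random class from each year group is selected to take part in the SLASF Comprehensive". The same section explains that classes are mixed-ability tutor groups.

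**The concern.** A school-level factor is estimated from schools, however many students each one holds. In the intervention arm each type is represented by a single school. A difference between the DEIS school and the mainstream mixed school therefore cannot be told apart from anything else peculiar to those two schools. The matched control schools help only for outcomes measured in them.

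A second, lesser issue concerns the students in the comprehensive sample, who enter as intact tutor groups. The programme also works partly through the class: section 2.5 describes class representatives and class tug-of-war teams. Correlated change within a class is therefore plausible. The levels that section 2.8.1 names are between and within individuals, plus school factors. If class is left out, its variation can appear as a school effect or make mean change look too precise.

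At stake is whether the report presents differences among a few particular schools as evidence on school factors or on theory, and whether that evidence then shapes the larger trial.

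**Working it through.** The protocol gives no intraclass correlation (ICC), power or sample size calculation for this model, so there is no figure of its own to reproduce.

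**Inputs from the protocol**
- Intervention schools: 3, one per type (sections 2.1 and 2.4). Control schools: 3, one per type, survey component only (section 2.2.1). Section 2.7 and Table 4 attach the DEIS label to different school letters, but the count per type is the same either way.
- Comprehensive sample (Table 4): 100 + 150 + 150 = 400 in intervention schools; 123 + 121 + 88 = 332 in control schools; 732 in all.
- One tutor group per year group in each school (section 2.2.2).

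**Assumptions**
- Six year groups per school, so 3 × 6 = 18 intervention classes and 400/18 ≈ 22.2 students per class.
- ICC for class between 0.02 and 0.10.
- Device data come from the three intervention schools only, as section 2.2.1 implies.

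**1. School-level degrees of freedom (df), device outcomes.** Intercept + DEIS + girls-only = 3 parameters. Residual df = 3 − 3 = 0.

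**2. School-level df, survey outcomes.** Intercept + two type terms + arm = 4 parameters. Residual df = 6 − 4 = 2, with a two-sided 5% critical t of 4.30. Letting the arm effect differ by type adds two parameters: 6 − 6 = 0.

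**3. Between-school variance.** The 95% limits as multiples of the estimate are (k − 1)/χ² at the upper and lower 2.5% points. They are optimistic, because no df is spent on type or arm.
- k = 3: 2/7.378 = 0.27 and 2/0.0506 = 39.5.
- k = 6: 5/12.83 = 0.39 and 5/0.831 = 6.0.

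A simulation (5,000 runs, Table 4 sample sizes, true school ICC 0.05, no class effect) agrees. With three schools, 95% of estimated ICCs lie between 0 and 0.18, and about 12% are exactly zero. With six schools the range is 0.001 to 0.13.

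**4. Ignoring tutor group: overall means or predictors constant within class.** The design effect is DE = 1 + (m − 1) × ICC with m = 22.2. The actual size of a nominal 5% test is 2 × [1 − Φ(1.96/√DE)].

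| ICC | DE | 400/DE | Actual size |
|---|---|---|---|
| 0.02 | 1.42 | 281 | 10% |
| 0.05 | 2.06 | 194 | 17% |
| 0.10 | 3.12 | 128 | 27% |

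For mean change, the relevant ICC is that of the change score, which the protocol does not give.

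**5. Ignoring tutor group: predictors that vary within class.** DE is roughly 1 + (m − 1) × ICC(outcome) × ICC(predictor). With both ICCs at 0.02, 0.05 or 0.10:
- 1 + 21.2 × 0.0004 = 1.01, actual size 5.1%
- 1 + 21.2 × 0.0025 = 1.05, actual size 5.6%
- 1 + 21.2 × 0.01 = 1.21, actual size 7.5%

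**6. Class variation appearing as a school effect.** The same simulation with no true school effect, six classes per school and class ignored gives these rejection rates for a nominal 5% test of school differences:

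| Class ICC | Three schools | Six schools |
|---|---|---|
| 0.02 | 12% | 16% |
| 0.05 | 23% | 35% |
| 0.10 | 38% | 58% |

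**The case against.** The strongest reply has four parts.

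*School factors may mean something else.* Section 2.8.1 speaks of school-related factors as independent variables, and Table 3 lists belonging, school satisfaction, perceived performance and similar items that each student answers. These vary within schools, and three schools are enough to estimate their student-level associations. This stands, and limits the point to the school-level component. It does not remove the point, because the sentence sets individual against school as sources of variation and the next paragraph compares schools.

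*There are control schools.* A reader might infer that nothing at school level has any degrees of freedom. The protocol does not support that: survey outcomes have two schools per type and keep 2 df after type and arm. The information is very weak, but it is not zero.

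*The tutor-group part argues from silence.* This is a condensed article, and the random-effects structure may be set out in a plan that is not shown. A reader might infer that students in a class are treated as independent, but the article does not say so. This stands, so that part is secondary and conditional. What remains is that the levels listed leave out the unit sampled. A reader might also apply the 10% to 27% error rates to every student-level association. They hold only for overall means, mean change or predictors constant within class; for predictors varying within class, step 5 gives about 5% to 7.5%.

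*It is optional and exploratory.* This also stands and lowers the severity. The primary objective in section 1.4 is acceptability, and no stopping criterion in Table 1 names this model or a test of school factors. A reader might infer that the decision to stop, revise or proceed is compromised; nothing in the protocol makes that decision depend on it. Even so, exploratory status does not fit with a claim to confirm theory.

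**Conclusion.** The claims to examine individual against school factors, and to confirm theory through between-context interactions, go beyond the design at school level. No separate analysis plan can cure this, because it cannot add schools. For device-based outcomes the confounding of school with school type is complete. For survey outcomes it is partial, but a contrast with 2 df and a critical t of 4.30 gives little basis for inference, and an arm-by-type interaction leaves no df. If accelerometers were in fact also worn in control schools, device outcomes would move to the six-school case, and the conclusion would weaken but not reverse.

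The tutor-group point is secondary. Its size, a design effect of about 1.4 to 3.1, rests on an assumed ICC of 0.02 to 0.10 and six year groups per school. It applies if class is in fact left out, and to mean change or class-constant comparisons.

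Overall the point is minor to moderate.

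**What to change.** In section 2.8.1:

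1. Enter school as a fixed effect and report school differences descriptively, school by school, without tests of school type.
2. Limit inference to student-level associations, including those with the student-reported school items, and to change within students.
3. Model occasions within students within tutor groups. Use random intercepts for student and class, and a class-by-time term where change is the target. Enter year group as a fixed effect. One class per year group makes class and year group coincide within a school, so class variance must be pooled across schools. With additive school and year-group effects and six year groups, 18 − (1 + 2 + 5) = 10 df remain for class in three schools. In six schools sampled the same way, 36 − (1 + 5 + 5) = 25 remain.
4. Use small-sample degrees of freedom (Kenward–Roger or Satterthwaite).
5. Delete the claim to separate school from individual factors and the claim that between-context interactions confirm theory.

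The cost is a change of analysis wording. Class membership is known from the sampling, so no new data are needed. The price is wider intervals and no inference about school factors.
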